### Study assessments

#### Baseline

The number of residents, type of care home (nursing or residential) and Care Quality Commission rating will be recorded for each participating care home.

Data collected for all potentially eligible participants will include age, sex, an existing dementia diagnosis or a positive response to the case finding question used for the UK National Commissioning for Quality and Innovation (CQUIN), ‘*has the person been more forgetful in the last 12 months to the extent that it has significantly affected their daily life?*’.^14^ For residents who are subsequently recruited into the study, a validated screening instrument for cognitive impairment comprising 10 questions, the Abbreviated Mental Test Score (AMTS), will be performed at baseline.^15^ A baseline CAM will also be performed.

#### Study assessments

Two delirium assessment instruments will be used throughout the 9 months of the study. These are the CAM performed two times per week by research staff and the 25-item DOSS performed once daily by care home staff, embedded into routine care. In contrast to the 13-item DOSS, the 25-item DOSS includes behaviours which span a full 24-hour period (ie, including night-time behaviours). If care home staff reflect back on a resident's behaviour over the course of a shift and use additional information obtained from care home records and handovers, it should be possible to identify whether there have been fluctuations in a resident's behaviour without the need to perform more than one DOSS assessment per day. Care home staff will be blinded to CAM assessments, and research assistants will be blinded to DOSS assessments, which will be stored separately from the care home record. Since symptom fluctuation is one of the diagnostic criteria for delirium, testing the sensitivity and specificity of the DOSS against the CAM relies on measurements being made close together such that variation is not falsely attributed to the instruments. The nearest date and timed DOSS measurement will be tested against the research assistant-administered CAM.

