### Sample size calculation

Measurement of sensitivity of the DOSS requires identification of cases where CAM and DOSS are positive. Sample size calculation is therefore based on the number of positive delirium episodes (identified with the researcher-administered CAM) required to measure the sensitivity of the DOSS with 95% confidence that the observed value is within 95% of the true value. Using the pooled estimate for sensitivity (92%) of the DOSS from previous studies,^9^ and the normal approximation to the binomial proportion distribution, there would need to be 113 measurements of CAM positive delirium during the study period.

The study involves repeated assessments; there is therefore likely to be correlation between serial CAM measurements. An episode of delirium lasts, on average, 11 days in the long-term care setting.^22^ CAM measurements are 4 days apart. It is likely that there will be at least two CAM measurements during each episode of delirium. We have therefore assumed at least moderate correlation between CAM measurements (intraclass correlation coefficient of 0.5). Applying an inflation factor (of 1.5) to account for the study design effect due to the repeated measures would require 170 CAM positive measurements over the 9-month study period. A recent study of delirium in Canadian long-term care settings offers the best available estimate of delirium incidence in care homes of 21.8% in 24 weeks.^1^ We estimate that 170 CAM positive readings would be made in 258 residents over 36 weeks.

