## Ethics and dissemination

The aim of this study is to identify delirium in a population at high risk from the condition. It is likely that this will increase the diagnosis of delirium in care homes. This may increase the requirement for medical assessment and input (eg, from general practitioners). General practitioners will be informed in writing when one of their patients is recruited into the study. Where a diagnosis of delirium is made by the research assistant (with the CAM), the care home manager will be informed in writing on the same day, such that appropriate action may be taken according to local procedures.

Results of the study will be published in peer-reviewed scientific journals. Reports will be prepared for, and disseminated to, Leeds, Bradford and York Clinical Commissioning Groups (CCGs), local General Practitioners, Age UK and the British Geriatrics Society. Lay summaries will be sent to participant care homes for dissemination to staff, residents and relatives.

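### DOSS raters are stated to be blind to the CAM, yet each CAM diagnosis is reported to the care home manager the same day, so at least half of the CAM-positive readings may be paired with a DOSS that is no longer blind

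*Protocol article*

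**What the plan says.** The article makes four statements that bear on this point.

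- **Blinding** (Study assessments): "Care home staff will be blinded to CAM assessments, and research assistants will be blinded to DOSS assessments". The only safeguard described is that DOSS forms are kept apart from the care home record.
- **Notification** (Ethics and dissemination): "Where a diagnosis of delirium is made by the research assistant (with the CAM), the care home manager will be informed in writing", and this happens "on the same day, such that appropriate action may be taken according to local procedures".
- **Sources for the DOSS** (Study assessments): one DOSS per day is held to be enough to pick up fluctuation if staff think back over the shift and "use additional information obtained from care home records and handovers".
- **Pairing** (Study assessments): "The nearest date and timed DOSS measurement will be tested against the research assistant-administered CAM". Nothing requires the DOSS to come before the CAM or before the notice.

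The schedule is "the CAM performed two times per week by research staff and the 25-item DOSS performed once daily by care home staff". The Sample size calculation section counts repeated CAM-positive readings within an episode towards the 170 from which sensitivity is estimated.

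**The concern.** The blinding statement and the notification rule do not fit together as written. A notice sent so that the home can act may well reach the staff who look after the resident, and those staff score the DOSS. Two kinds of pair are exposed. The first is a first positive CAM whose nearest DOSS was scored after the notice. The second is any later positive CAM in the same episode, because the home has by then been told of that episode.

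Both kinds lie among CAM-positive readings, which form the denominator of sensitivity, and sensitivity is the quantity the study is sized on. A rater who knows the reference result is likely to score towards it. The study could then credit care home staff with detecting delirium unaided in residents whose diagnosis had already been passed to the home.

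**Working it through.** **Inputs.** From the Sample size calculation section: sensitivity 92%, 113 readings, ICC 0.5, inflation 1.5, 170 readings, mean episode 11 days, CAMs 4 days apart, at least two CAMs per episode, incidence 21.8% in 24 weeks, 258 residents, 36 weeks. From the Introduction: 95% CI of 74% to 98% for pooled DOSS sensitivity. Assumed, not in the documents: an informed rater scores positive 98% of the time, and every later rater is informed.

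**1. The plan's own figures.**
- n = 1.96² × 0.92 × 0.08 / 0.05² = 113.1, which matches 113. The planned precision is therefore 5 percentage points either side.
- Design effect = 1 + (m − 1) × ICC = 1 + (2 − 1) × 0.5 = 1.5, and 113 × 1.5 = 169.5, which matches 170.
- Episodes = 258 × 0.218 × 36/24 = 84.4. At two readings each this gives 168.7, close to 170.

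Both the inflation factor and the number of residents therefore imply m = 2 CAM-positive readings per episode.

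**2. Share of CAM-positive readings that follow a notice about the same episode.** With m positive readings per episode, all but the first come after a report, so the share is 1 − 1/m.

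| Basis | m | Share | Of 170 |
|---|---|---|---|
| Plan's minimum | 2 | 50% | 85 |
| 11 days / 4 days | 2.75 | 64% | 108 |
| 11 days / 3.5 days (exactly twice weekly) | 3.14 | 68% | 116 |

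These are shares exposed to a notice, not shares shown to be unblinded. First positives paired with a DOSS scored after the notice would add to them; the article does not allow that number to be worked out.

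**3. Illustrative bias.** Observed sensitivity = (1 − share) × s + share × 0.98, so bias = share × (0.98 − s), where s is the true unaided sensitivity.

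| True s | Bias at 50% | Bias at 64% |
|---|---|---|
| 92% (plan's value) | +3.0 points | +3.8 points |
| 80% | +9.0 points | +11.5 points |
| 74% (lower limit in the Introduction) | +12.0 points | +15.3 points |

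At a share of 68% and s = 92% the bias is +4.1 points.

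**4. Precision from first positives only.** One reading per episode leaves about 85 (170 / 2). Half-width = 1.96 × √(0.92 × 0.08 / 85) = 5.8 points, against 5.0 as planned.

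**The case against.** The notice goes to the manager, and the article does not say that raters are told. What the manager passes on is a detail that a full protocol may settle. The sentence on records and handovers is conditional and explains why one DOSS a day may suffice; it does not instruct raters to look for the CAM result. All this stands. A reader might infer that half or more of the sensitivity estimate is known to come from unblinded scores. The documents do not support that: they show that those readings follow a notice and that no barrier is described.

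The size is also open. The 98% is an assumption. At the plan's 92% the illustrated bias is below the 5-point planned precision. A reader might infer a bias as large as +19 points, but that needs a true sensitivity of 70% (0.68 × 0.28), below the 74% lower limit quoted in the Introduction. The DOSS is 25 yes/no items on observed behaviour, probably less open to suggestion than an overall diagnosis. The cut-point is to be chosen from the ROC curve, so a shift in scores need not act on sensitivity alone.

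Nor is the direction certain. Action after a notice could improve the resident and lower later DOSS scores, and knowledge of a past positive could raise scores after recovery and affect specificity. Upward bias in sensitivity remains the likelier result.

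Finally, nearest-in-time pairing was chosen because delirium fluctuates. Making first positives with only a prior DOSS the sole primary estimate would be a debatable trade against that aim. This stands and has shaped the fix. None of it removes the conflict between the two sections.

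**Conclusion.** The point holds as a conflict in the text with a plausible effect on the main estimate. Unqualified blinding of DOSS raters cannot be assumed alongside same-day reporting of each CAM diagnosis to the manager, when no barrier is described and the pairing rule ignores the timing of the notice.

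On the plan's own figures, at least half of CAM-positive readings (50% at two per episode, about 64% at 4-day spacing) follow a notice about the same episode. Up to that share, plus any first positive paired with a later DOSS, may come from raters who are no longer blind. This rests on each reading in the episode being CAM-positive and reported.

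The likely direction is inflated sensitivity. The amount is unknown: about +3 to +4 points at a true 92% if all later raters are informed and score positive 98% of the time, more if true sensitivity is lower, and less if few raters learn of the notice. Recruiting more residents would not remove it.

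**What to change.** Leave the notification as it is. Change the wording and the analysis.

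1. In Study assessments, say that rater blinding cannot be assumed once a positive CAM has been reported, and reconcile this with Ethics and dissemination. If there is a barrier between the manager's notice and the raters, describe it.
2. Keep nearest-in-time pairing, but for a CAM-positive reading accept only a DOSS completed before that CAM's notice was given. This needs the time of the notice to be logged.
3. Pre-specify sensitivity for the first CAM-positive reading of each episode, with a rule for when a new episode starts. Report it alongside the all-readings estimate, and show later readings of notified episodes separately. Rest any claim about unaided detection on the first-positive result. Comparing the two sets gives some indication of whether notification mattered.

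**Cost.** No extra assessments are needed. The first-positive estimate uses about 85 readings, fewer than the plan's 113, so its half-width is about 5.8 points instead of 5.0. Some CAM-positive pairs will have a somewhat longer gap between DOSS and CAM. Where delirium begins between the two, the DOSS will be counted as a miss, which may bias first-positive sensitivity downwards. Reporting both estimates lets the reader weigh this against the likely upward bias of the all-readings figure.

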For an instrument to have utility for delirium detection in routine care in the care home setting, it should be brief and not require specialist knowledge or training to administer. It should have high sensitivity (a low false-negative rate), and acceptable specificity (a high true-negative rate).

Fourteen reviews of delirium assessment instruments have identified six externally validated instruments that may be administered by nursing staff. Of these, two may have utility as screening tools for delirium in the care home environment. These are the Delirium Observation Screening Scale (DOSS)^7^ and the Nursing Delirium Screening Scale (NuDESC).^8^ Sensitivity of the DOSS is comparable with the NuDESC for detection of delirium (pooled sensitivity for the DOSS is 92% (95% CIs 74% to 98% 2 studies, 178 participants) vs 96% for the NuDESC (95% CI 80% to 100% 1 study, 100 participants)).^9^ However, the specificity of the DOSS is higher (82% (95% CI 66% to 92%) vs 69% (95% CI 59% to 79%)); therefore, the DOSS was chosen as the candidate instrument for the study. The DOSS comprises items which seek objective assessment of the behavioural aspects of the DSM-IV delirium diagnostic criteria: onset of a short period of altered consciousness; reduced ability to focus, sustain or shift attention; a change in cognition (memory deficit, disorientation, language disturbance); and perceptual disturbance not better accounted for by a pre-existing, established or evolving dementia. The DSM also stipulates that, for a diagnosis of delirium, there is evidence from the clinical assessment that these changes are associated with a general medical condition and that there is fluctuation during the course of the day.

The psychometric properties of the DOSS have been assessed in acute and rehabilitation settings,^7^
^10^ but the utility of the DOSS in care homes has not been evaluated. This study aims to determine how the DOSS performs as a screening instrument for delirium when administered by care home staff in comparison to a research standard assessment based on the Confusion Assessment Method (CAM).^11^

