## Methods and analysis

The DOSS study is a prospective observational cohort study, performed in UK long-term care settings over 24 months (May 2014 to May 2016). The 25-item DOSS, performed once daily by care home staff, will be measured against the temporally closest CAM (a research standard) performed two times per week by research staff for all participants. Feasibility of routine daily administration of the DOSS will be investigated by examining patterns and rates of missing data on care home staff completed DOSS assessments. To determine the diagnostic test accuracy of the DOSS, sensitivity, specificity, positive and negative predictive values and likelihood ratios of the DOSS for the detection of delirium will be calculated. The CAM has been validated as a measure of delirium severity^12^ and this will allow for a further investigation to determine whether the DOSS may also be used as a measure of delirium severity. Repeated daily DOSS measurements will be used to examine the scaling properties of the 25-item DOSS instrument. Item response theory will be used to determine whether the questions are measuring the same underlying constructs (delirium) and whether there are any redundant questions which may be removed to create a shorter, care home-specific DOSS.^13^

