### Data analysis plan

We aim to evaluate the feasibility of embedding the existing DOSS instrument into routine care rather than to evaluate the content of the questionnaire. Feasibility of administration of the DOSS by care home staff will therefore be examined through exploring the rates of missing data, and by examining the intraclass correlation coefficients between staff-administered DOSS assessments.

A receiver operating curve will be plotted to determine the optimal cut-point for the 25-item DOSS. Sensitivity, specificity, positive and negative predictive values, likelihood ratios positive and negative, and a diagnostic OR will be calculated with 95% confidence limits.

Correlation of the 25-item DOSS with the CAM severity score will be used to determine whether the DOSS may be used as a marker of delirium severity.

Item response theory (non-parametric and parametric if appropriate) will be performed to determine the scaling properties of the 25-item DOSS and to identify whether there are any redundant items to form a care home-specific version of the DOSS.

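### The DOSS–CAM pairing rule has no time limit and missing forms count only towards feasibility, so sensitivity describes completed forms, not what staff screening flags on each CAM occasion

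*Protocol article*

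**What the plan says.** The pairing is stated twice, in opposite directions. Study assessments starts from the CAM: "The nearest date and timed DOSS measurement will be tested against the research assistant-administered CAM". Methods and analysis starts from the DOSS, which is "performed once daily by care home staff, will be measured against the temporally closest CAM". Neither gives a longest allowed gap. Just before its rule, Study assessments says that testing the DOSS against the CAM "relies on measurements being made close together such that variation is not falsely attributed to the instruments".

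Missing forms are assigned to feasibility in both places that mention them. Methods and analysis: "Feasibility of routine daily administration of the DOSS will be investigated by examining patterns and rates of missing data". Data analysis plan: "Feasibility of administration of the DOSS by care home staff will therefore be examined through exploring the rates of missing data". The Data analysis plan then lists sensitivity, specificity and the other accuracy measures, and does not say what happens to a CAM with no DOSS close to it.

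The aim in the Introduction is to learn "how the DOSS performs as a screening instrument for delirium when administered by care home staff", with the CAM as the comparator.

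**The concern.** A nearest-form rule with no limit always finds a partner for a CAM, provided the resident has at least one form. If staff did not complete the form close to a positive CAM, a form from another day is used, and the omission is neither a lost pair nor a missed case. Two things follow.

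- The rule does not secure the closeness that the protocol says the comparison needs. Delirium fluctuates, so a form from another day may describe a different state.
- Completion and accuracy are never joined. A home could show good accuracy on completed forms and a good completion rate while a clearly smaller share of CAM-positive occasions had a positive form. An overall completion rate would not show this, because CAM-positive occasions are a very small part of all readings.

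At stake is the conclusion about routine screening by staff, which needs both parts. The two pairing directions also produce different data sets: one pair per CAM, or one pair per completed form with several forms sharing a CAM.

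**Working it through.** **Inputs from the protocol.** Sensitivity 92%, required CAM-positive readings 113 and then 170, inflation factor 1.5, mean episode 11 days, incidence 21.8% in 24 weeks, 258 residents over 36 weeks (Sample size calculation); pooled specificity 82% (Introduction); two CAMs per week (Study assessments).

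**Assumption.** *c* is the probability that a CAM-positive occasion has its own DOSS form. The protocol gives no value, so a range is shown.

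**1. The plan's own figures.** The sample size rests on "Using the pooled estimate for sensitivity (92%) of the DOSS from previous studies" and on precision "with 95% confidence that the observed value is within 95% of the true value", read here as a half-width of 5 percentage points.
- 1.96² × 0.92 × 0.08 / 0.05² = 113.1, stated as 113.
- Two readings per episode with correlation 0.5: 1 + (2 − 1) × 0.5 = 1.5, and 113 × 1.5 = 169.5, stated as 170.
- Residents: 0.218 × 36/24 = 0.327, and 170 / (2 × 0.327) = 259.9, against 258 stated.

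These reproduce. None contains a term for missing DOSS forms.

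**2. Share of readings that are CAM-positive.** 258 × 36 × 2 = 18,576 readings, and 170 / 18,576 = 0.9%. If completion were 80% in general but 67% on CAM-positive occasions, the overall rate would move by about 0.009 × 13 = 0.1 point.

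**3. Three versions of sensitivity.**
- *Same-day completed forms:* 92% at every *c*, if missingness is unrelated to the result.
- *Nearest-form rule:* 0.92*c* + (1 − *c*) × *s*, where *s* is the chance that the stand-in form is positive. For a form one day away, with exponential episode length (an assumption), the resident is also delirious that day with probability exp(−1/11) = 0.913, so *s* = 0.913 × 0.92 + 0.087 × 0.18 = 0.856. For more distant forms, *s* = 0.70 and 0.50 are assumed.
- *Flagged per CAM occasion, no form counted as not detected:* 0.92*c*.

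| *c* | Nearest form, one day away | Nearest form, *s* = 0.70 | Nearest form, *s* = 0.50 | Flagged per occasion |
|---|---|---|---|---|
| 0.95 | 91.7% | 90.9% | 89.9% | 87.4% |
| 0.90 | 91.4% | 89.8% | 87.8% | 82.8% |
| 0.80 | 90.7% | 87.6% | 83.6% | 73.6% |
| 0.60 | 89.4% | 83.2% | 75.2% | 55.2% |

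Stand-in forms pull the figure below 92%, but in every row it stays above the per-occasion share.

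**4. Per episode.** Take *c* = 0.60 and daily forms over 11 days. The chance of at least one positive form is 1 − (1 − 0.552)¹¹ = 99.99% if days are independent, and 0.92 × (1 − 0.4¹¹) = 92.0% if the DOSS result is constant within an episode. Over the first two days the same formulas give 79.9% and 77.3%.

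**5. Missingness related to the result.** Among CAM-positive occasions, completion of 0.9 for would-be positive forms and 0.6 for would-be negative ones gives 0.828 / (0.828 + 0.048) = 94.5%. The reverse gives 0.552 / (0.552 + 0.072) = 88.5%.

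**6. Precision if only pairs within the interval are kept.** The half-width is 1.96 × √(0.92 × 0.08 / (170*c*/1.5)): 5.0 points at *c* = 1, 5.6 at 0.80 (136 pairs) and 6.4 at 0.60 (102 pairs).

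**The case against.** The strongest case against is that this is a test-accuracy study with feasibility as a separate objective. Accuracy on completed forms, reported beside a completion rate, is a legitimate design, and nothing in the protocol says that sensitivity will be presented as the share of delirium a screening programme detects. That stands, and it is why the fix keeps the completed-form figure. Methods and analysis also promises patterns as well as rates of missing data, which could include completion by CAM status. But nothing commits to that, and the Data analysis plan mentions only rates.

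It can also be said that time windows and missing-data handling belong in an analysis plan that is not shown. In general they do. Here, though, the article itself fixes the rule, in two directions and without a limit, beside its own requirement of closeness.

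A reader might infer more than the documents support:

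- *That the nearest-form rule inflates sensitivity.* Against same-day accuracy, step 3 shows the opposite. The gap to the per-occasion figure comes from non-completion and would remain if stand-in forms were banned.
- *That the sensitivity overstates what daily screening detects in general.* Step 4 shows that this need not hold per episode, because daily forms give repeated chances. It holds per occasion, and for detection in the first two days at 60% completion.
- *That forms go missing more often when residents are delirious.* No passage says so, and step 5 shows that missingness related to the result can move the estimate either way.
- *That a form completed after a positive CAM is influenced by the same-day notice to the care home manager (Ethics and dissemination).* Study assessments says staff are blinded to the CAM, and no passage says the notice reaches those who complete the form.

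A strict same-day restriction would be hard to defend: a form from the previous evening can be closer to a morning CAM than one completed late the same day. A window in hours avoids this.

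**Conclusion.** The concern holds in a limited form. The pairing rule is open-ended and worded in two directions, and it does not secure the closeness on which the protocol says the comparison relies. Missing forms enter only the feasibility result. The sensitivity therefore describes completed forms, somewhat diluted by any stand-ins, and per CAM occasion it exceeds the share of delirium that staff screening flags. Taking the protocol's 92% for same-day forms, the excess is 4.6 points at 95% completion, 18.4 at 80% (92% against 73.6%) and 36.8 at 60%. These sizes rest wholly on assumed completion rates; if nearly every CAM-positive occasion has a form, the issue is small. The point does not show that the instrument's accuracy is overestimated or that episodes would go undetected.

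**What to change.** In Methods and analysis and in Study assessments, state one pairing direction and a maximum DOSS–CAM interval, for example within 24 hours. Starting from the CAM fits the sample size, which counts CAM-positive readings.

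In the Data analysis plan:

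- report DOSS completion within the interval separately for CAM-positive and CAM-negative occasions;
- give sensitivity on paired forms and, beside it, sensitivity with CAM-positive occasions lacking a form in the interval counted as not detected, labelled as per-occasion detection;
- use both figures when concluding on routine screening.

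No new data are needed. The costs are some lost pairs (half-width from about 5.0 to 5.6 points at 80% completion) and a second figure that looks less favourable and gives no credit for later detection within the same episode. The label should say so.
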